### Eligibility criteria

Cases: All participants aged ≥18 years who are hospitalized due to the first occurrence of an acute myocardial infarction (AMI), stroke, or peripheral artery thrombotic event, presenting in the first 7 days from symptom onset will be screened (S3 File).

Eligible cases must have signs and/or symptoms compatible with the acute manifestation of ASCVD. Case definitions include diagnostic criteria based on national and international guidelines. Acute myocardial infarction is defined as: clinical presentation, electrocardiogram patterns (new pathological Q waves, and/or ST-segment elevation of 1 mm in ≥ 2 contiguous leads, or 2 mm from V1 to V3, or new left bundle branch block, or new changes in the ST-T segment, and cTnI or cTnT curve compatible with acute myocardial injury of ischemic nature (which is currently named a type 1 acute MI). Stroke is defined as clinical signs of rapid development of focal or global brain function disorder, lasting more than 24 hours, with no apparent cause other than that of vascular origin (does not include trauma, cancer, infection of the central nervous system), and Computed Tomography or Magnetic Ressonance Imaging with positive results. Peripheral artery thrombotic event is defined as clinical presentation (pain, burning sensation, absence of pulse, decreased local temperature, changes in color) and diagnostic tests (Doppler ultrasound, angiotomography, or arteriography) that show interruption of flow to the lower limbs acutely, of embolic or thrombotic cause, leading to distal ischemia [20–23].

Controls: All participants aged ≥18 years seeking medical care for non-ASCVD conditions will be screened and enrolled during hospitalization; and healthy individuals with no clinical complain will also be screened and enrolled at the same community. Cases and controls will be recruited in a 1:1 ratio adjusted for sex and age.

Exclusion criteria for both cases and controls are previously known ASCVD, e.g., chronic coronary artery disease, stable angina, previous myocardial infarction, percutaneous revascularization procedures (coronary, cerebrovascular, or peripheral), surgical revascularization procedures in any arterial vascular bed, transient ischemic attack, stroke, aortic aneurysm, intermittent claudication, peripheral artery disease that led to amputation.

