### Sample size calculation

We applied the following statistical assumptions: odds ratio for genetics was set at 1.3, allele frequency of 10%, inheritance model was dominant (since the presence of only one polymorphic allele is required to the risk calculation), the prevalence of CVD in the general population of 10%, statistical power of 90%, type I error rate (α) of 0.05, 2-sided significance tests, resulting in a sample of 1,867 cases and 1,867 controls. Sample size calculation was performed using Quanto Software Version 1.2.4.

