### Variables

The exposure to modifiable risk factors in combination with genomic data (polygenic risk score) in both cases and controls will be expressed as odds ratios (95% CI). Multiple logistic regression models will be built to adjust and determine the strength of association between demographic variables (sex, age, race), traditional risk factors (smoking, diabetes, hypertension, obesity, anxiety and depression, unhealthy diet, physical inactivity, alcohol consumption, and apolipoprotein B/A1 ratio [ApoB/ApoA1], and genetic data [PRS]. For each variable with a higher chance of CVD (significant OR), attributable risk estimate will be calculated for the genetic component (PRS) and other covariables. Fig 2 shows the Polygenic Risk Score flowchart.

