### Data analysis

#### Quantitative variables and statistical analysis

The Hardy-Weinberg genetic equilibrium test will be evaluated in the control group using the chi-square test or Fisher’s exact test. To estimate the association between genetic polymorphisms and risk of CVD, univariate and multiple unconditional logistic regression analyses will be conducted [32–36].

Initially, univariate binary logistic regression analyses will be performed. Thus, covariates with a p-value < 0.20 in univariate regression analyses will be considered in multiple logistic regression analysis with selection of variables according to the backward elimination technique [37, 38]. The selection process in the backward elimination allows the sample size to adjust and always uses the maximum available sample as the number of variables in the model drops [37]. Occasionally, covariates judged as confounding factors by the investigator may be forced into the final backward regression model.

Additional multiple logistic regression analyses may also be conducted using a variant of the Purposeful Selection algorithm described by Bursac *et al*. [38].

The assumption of linearity on the logit scale (log-odds) between each quantitative covariate and the binary response variable in binary logistic regression analysis will be evaluated with the construction of “Smoothed Scatter Plots” and the method of fractional polynomials [35–39]. When the assumption is not satisfied, quantitative covariates will be categorized for use in logistic regression using cut-off points, according to the literature, distribution tertiles or optimal cut-off obtained from the Receiver Operating Characteristic (ROC) curve, whichever is deemed most appropriate. In case of an optimal cut-off point, it will be defined as the one that maximizes the Youden index [39, 40].

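### The univariate p<0.20 screen is likely to remove sex and age, which recruitment balances, and only an optional clause would keep them in the model

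*Protocol article*

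**What the plan says.** The Eligibility criteria section states: "Cases and controls will be recruited in a 1:1 ratio adjusted for sex and age". It gives no caliper, age band or pairing rule.

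Under Quantitative variables and statistical analysis, "univariate and multiple unconditional logistic regression analyses will be conducted". Entry to the multiple model is decided by a screen: "covariates with a p-value < 0.20 in univariate regression analyses will be considered in multiple logistic regression analysis". Backward elimination follows. Two provisions soften this:

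- A discretionary override: "Occasionally, covariates judged as confounding factors by the investigator may be forced into the final backward regression model".
- An optional second selection method, offered alongside the main one: "Additional multiple logistic regression analyses may also be conducted using a variant of the Purposeful Selection algorithm".

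Neither provision names sex or age.

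The Variables section reads differently. It says "Multiple logistic regression models will be built to adjust and determine the strength of association between demographic variables (sex, age, race", and goes on to the traditional risk factors and the polygenic risk score (PRS). For variables with a significant odds ratio (OR), an "attributable risk estimate will be calculated for the genetic component (PRS) and other covariables". The Bias control section also relies on adjustment through multivariate logistic models.

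**The concern.** Once recruitment has balanced sex and age, their univariate p-values show how well the balancing worked. They do not show whether adjustment is needed. A significance screen is therefore the wrong gate for these two factors, and the stated default probably removes variables that the Variables section places in the models.

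Unconditional regression on a sample balanced on sex and age is sound if those factors are in the model. If they are left out, the OR of any exposure that varies with age or sex is pulled toward 1, and so is the population attributable risk (PAR) built on it. Hypertension, diabetes, smoking and lipids are plausible examples. The Discussion sets a genetic PAR beside the PAR of modifiable factors, so understating the modifiable side would distort that comparison even if the genetic estimate is sound.

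**Working it through.** **1. The plan's own figure.** From the Sample size calculation section: "odds ratio for genetics was set at 1.3", allele frequency 10%, dominant model, prevalence 10%, 90% power, two-sided 0.05.

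- Carrier frequency = 1 − 0.9² = 0.19.
- Solving for 10% prevalence gives carrier rates of 0.2287 in cases and 0.1857 in controls. Check: (0.2287/0.7713)/(0.1857/0.8143) = 1.30.
- Unmatched likelihood-ratio formula: n per group = (1.960 + 1.282)²/L, where L is the likelihood-ratio statistic per case plus control. The result is 1,866.7, which rounds up to the stated 1,867.
- The matched-pair likelihood-ratio version gives about 1,869.

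The sample size is reproduced and does not depend on this point.

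**2. What a factor needs to pass p<0.20.** The two-sided critical value is 1.2816, with 1,867 per group.

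- Age, assumed SD 12 years: 1.2816 × 12 × √(2/1,867) = 0.50 years between group means.
- Sex, assumed 60% male: 1.2816 × √(2 × 0.6 × 0.4/1,867) = 0.0205, about 2.1 percentage points.

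**3. Chance that age passes the screen.** The matching rule is not stated, so several were simulated (assumed age SD 12).

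| Assumed scheme | Age passes | Age removed |
|---|---|---|
| Individual matching, exact or within 2, 5 or 10 years | 0% | 100% |
| 2- or 5-year bands, younger control source | 0% | 100% |
| 10-year bands, younger control source | about 37% | about 63% |
| Same distribution only, independent draws | 20% | 80% |

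The last row follows from the definition of p<0.20 and holds for sex as well. If the two factors are independent, both are removed with probability 0.8 × 0.8 = 0.64. These chances concern the screen alone. A factor that passes must still survive backward elimination, which was not modelled.

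**4. Effect of omission, closed form.** Assumptions: three age bands holding 15%, 45% and 40% of cases, controls matched to them, and a true OR of 2.5 in each band. With w the band share, p0 the control prevalence in a band and pc = 2.5·p0/(1 − p0 + 2.5·p0):

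crude OR = odds(Σw·pc)/odds(Σw·p0); PAR = (Σw·pc) × (1 − 1/OR).

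Worked case, control prevalence 8/35/65%:

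- Σw·p0 = 0.0120 + 0.1575 + 0.2600 = 0.4295.
- Σw·pc = 0.0268 + 0.2582 + 0.3291 = 0.6141.
- Crude OR = (0.6141/0.3859)/(0.4295/0.5705) = 2.11.
- PAR = 0.6141 × (1 − 1/2.11) = 0.32, against 0.6141 × (1 − 1/2.5) = 0.37.

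| Control prevalence by band | OR without age (true 2.5) | Shrinkage | PAR without age vs correct |
|---|---|---|---|
| 3/15/25% | 2.37 | 5% | 0.19 vs 0.20 |
| 8/35/65% | 2.11 | 16% | 0.32 vs 0.37 |
| 5/35/75% | 1.95 | 22% | 0.31 vs 0.38 |

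**5. Effect of omission, large-sample simulation.** Controls were matched to cases within age-sex cells. Age (per SD) and sex were each given a log-odds of 0.7 for disease (assumed). The unconditional fit was made with and without age, age squared and sex.

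| Assumed exposure | True OR | OR without / with | PAR without / with |
|---|---|---|---|
| Genotype unrelated to age and sex | 1.3 | 1.30 / 1.30 | 0.053 / 0.053 |
| Weak age and sex link | 2 | 1.975 / 2.001 | 0.252 / 0.256 |
| Hypertension-like age link | 2 | 1.86 / 2.00 | 0.304 / 0.329 |
| Strong age link | 2 | 1.74 / 1.99 | 0.299 / 0.349 |
| Smoking-like link | 3 | 2.72 / 2.98 | 0.330 / 0.347 |
| Very strong age and sex link | 3 | 2.43 / 2.98 | 0.464 / 0.524 |

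Shrinkage runs from 1 − 1.975/2.001 = 1% to 1 − 2.428/2.978 = 18%. The PAR loss runs from 0.4 to 6.0 percentage points. With sex and age in the model, the true OR is recovered to within about 1%.

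**The case against.** A reader might infer that the screen must drop sex and age, that neither could ever reach p<0.20, and that the planned model therefore ignores the balancing factors. The article does not support that, for three reasons.

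- No matching rule is given. Loose balancing could let a factor through, as the 37% and 20% figures show. Unconditional regression fits frequency balancing better than individual pairs, and so, slightly, does a sample size that the unmatched formula reproduces exactly. Neither settles the matter.
- The force-in clause turns on the investigator's judgement, not on crude p-values. Sex and age are the covariates most likely to be judged confounders, so it cannot be assumed that the clause will go unused.
- The Variables section can be read as the candidate list and the Data analysis section as the selection procedure with an override. That leaves a tension unresolved; it does not fix an omission.

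It is also fair that the main target is the genetic association, which is unchanged if the PRS is unrelated to age and sex. The larger shrinkage figures need steep assumed gradients. The full protocol or analysis plan, not shown here, may fix the covariates.

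All of this limits the point but does not remove it. The article does not leave the selection rule open: it states one that tests sex and age by significance. The force-in clause is worded as occasional and permissive, and Purposeful Selection is only an additional option. These routes allow the right model without securing it.

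**Conclusion.** The point holds in limited form. The screen and backward elimination are the wrong gate for two factors balanced by design, and the screen is likely to remove them: certain or nearly so under close matching, and about 63% (age, 10-year bands) to 80% (either factor, equal distributions only) under the loose schemes assumed. Keeping them rests on an optional decision, which is at odds with the Variables section.

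Bias arises only if the factors are actually left out. It would then be modest in most scenarios: 1% to 18% on the OR in the simulations and 22% with the steepest closed-form gradient, with PAR losses of about 0.4 to 7 percentage points. It would fall on age- or sex-related risk factors and not on a PRS unrelated to age and sex. The age SD, the share of men, the matching schemes and the exposure gradients are all assumptions, because the article gives none of them. The direction toward 1 is consistent in every scenario where the exposure is linked to age or sex. This should be corrected because the remedy is so cheap, but it does not threaten the main genetic estimate.

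**What to change.** State under Quantitative variables and statistical analysis that sex and age, coded as in recruitment, are design variables. They stay in every multiple model and are exempt from both the p<0.20 screen and backward elimination. Word the Variables section to match. Use conditional logistic regression only if controls were individually paired to cases; with frequency balancing, the unconditional model containing both factors is adequate. If the full protocol or analysis plan already fixes these terms, aligning the article is enough.

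The cost is one sentence and two model terms (slightly more if age is coded in bands), with negligible loss of precision. Sex and age are already to be collected, no further participants are needed, and the sample size stays essentially the same (1,867 per group unmatched, about 1,869 pairs if matched).

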#### Bias control

Eligibility criteria for cases and controls will be strictly followed to reduce selection bias. The criteria defined for the first ASCVD event were standardized, and all sites have been trained for the correct identification, data recording, and reporting of information. Cases will be validated by the adjudication committee through clinical data, diagnostic tests, hospitalization and/or discharge summary, among others, using the standardized and validated process for diagnoses [45, 46]. The relationship between the variables will be adjusted by multivariate logistic models. Data monitoring will be applied throughout the entire study timeline to assure data quality. Blood and urine samples collection have been standardized, and genetic and biochemistry analyses will be performed in a core lab to guarantee the standardization of methods and quality control.

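### Obesity, diet, inactivity and alcohol share one data-selected model with hypertension, diabetes and ApoB/ApoA1, so their attributable risks are direct-effect remainders, understated to an unknown degree or not reported

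*Protocol article*

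**What the plan says.** The Variables section of the protocol article lists the covariates of the multiple logistic models together: demographics, the polygenic risk score (PRS) and "smoking, diabetes, hypertension, obesity, anxiety and depression, unhealthy diet, physical inactivity, alcohol consumption, and apolipoprotein B/A1 ratio". It then states which of them receive an attributable risk: "For each variable with a higher chance of CVD (significant OR), attributable risk estimate will be calculated for the genetic component (PRS) and other covariables".

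The section Quantitative variables and statistical analysis gives the model-building rule. Covariates with a univariate p-value below 0.20 "will be considered in multiple logistic regression analysis with selection of variables according to the backward elimination technique". It adds one exception: "Occasionally, covariates judged as confounding factors by the investigator may be forced into the final backward regression model". A variant of Purposeful Selection may be run in addition. Bias control says only that "The relationship between the variables will be adjusted by multivariate logistic models".

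The article does not separate upstream factors from the conditions through which they may act, and it describes no model for total effects. By the Introduction and Discussion, the main aim is the attributable fraction of the genetic profile, adjusted for modifiable factors. The attributable risks of the other covariables come in addition.

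**The concern.** Obesity, diet, inactivity and alcohol plausibly cause events partly by raising blood pressure, glucose and atherogenic lipids. That is subject-matter knowledge and not a statement in the protocol, but for obesity it is hard to contest. With hypertension, diabetes and ApoB/ApoA1 in the model, the coefficient of an upstream factor measures only what does not pass through them. An attributable risk computed from it is not the share of events that removing the factor would avoid.

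Two significance rules add to this. Backward elimination drops a factor whose residual effect is weak, and the Variables section then gives no attributable risk to a factor without a significant OR. The reader would see no figure at all, and could take that to mean that the factor contributes nothing in Brazil when the cause is the composition of the model.

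**Working it through.** **1. The plan's own figure.** Inputs from Sample size calculation: OR 1.3, allele frequency 10%, dominant model, CVD prevalence 10%, power 90%, two-sided α 0.05.
- Carrier frequency = 1 − 0.9² = 0.19.
- With the logistic intercept solved for 10% prevalence, carriers are 0.2287 of cases and 0.1857 of controls. Check: (0.2287/0.7713)/(0.1857/0.8143) = 1.30.
- The two-proportion formula gives 1,868 per group and the likelihood-ratio version 1,867. Power at 1,867 is 0.900.

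The stated 1,867 + 1,867 is reproduced. It was derived for a genetic OR and says nothing about modifiable factors, so here it only sets the size of the simulated samples.

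**2. Formula.** The article gives no formula for the attributable fraction. The usual case-control form is assumed: PAF = p_c × (OR − 1)/OR, where p_c is the share of cases exposed. Since p_c is the same in both models, the proportion lost depends only on the two ORs.

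**3. Assumed inputs (none are in the documents).**
- Prevalence of obesity, poor diet, inactivity and alcohol: 35, 40, 50 and 20%.
- ORs for CVD: hypertension 2.0, diabetes 2.3, high ApoB/ApoA1 2.5.
- ORs from upstream factor to mediator, weak to strong: obesity 1.3–3.0, diet and inactivity 1.1–1.5, alcohol 1.0–1.5.
- Selection: univariate p < 0.20, then backward elimination at p < 0.05, on 300 samples of 1,867 + 1,867 per scenario. The article states no threshold for staying in the model; 0.05 is taken from its general significance level. The Monte Carlo standard error of an elimination rate is at most √(0.5 × 0.5/300) ≈ 3 points.

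**4. Worked example: obesity, moderate paths, direct OR 1.1.** Without mediators the OR is 1.48 and the PAF 14.0%, so p_c = 0.140/(0.48/1.48) = 0.43. With mediators the OR is 1.11, giving 0.43 × 0.11/1.11 ≈ 4.3% (4.2% before rounding). Loss = 1 − 4.2/14.0 = 70%.

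**5. Obesity across scenarios.**

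| Paths | Direct OR | PAF without mediators | PAF mutually adjusted | Lost | Eliminated, with / without mediators in the model |
|---|---|---|---|---|---|
| strong | 1.0 | 14.8% | 0.6% | 96% | 96% / 0% |
| moderate | 1.1 | 14.0% | 4.2% | 70% | 70% / 0% |
| moderate | 1.2 | 16.5% | 7.2% | 56% | 35% / 0% |
| weak | 1.2 | 12.1% | 6.9% | 43% | 33% / 0% |
| moderate | 1.4 | 22.0% | 13.6% | 38% | 1% / 0% |
| weak | 1.4 | 17.7% | 13.0% | 27% | 0% / 0% |

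A separate simulation defined the true attributable risk by setting obesity to absent and letting the mediators respond. It assumed obesity prevalence 25%, hypertension and diabetes ORs of 2, ApoB/ApoA1 OR 1.5 per SD, and direct ORs of 1.1–1.2. True values of 8.1–15.3% fell to 2.4–6.2%. The smallest loss was 1 − 5.0/10.5 = 52% and the largest 1 − 2.4/8.1 = 70%.

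**6. The other upstream factors.** With direct ORs of about 1.15–1.25, the loss from weak to strong paths is 14–42% for diet, 13–32% for inactivity and 10–29% for alcohol. It passes half mainly for diet and inactivity with direct ORs of 1.1 or less. Elimination under moderate paths and direct ORs of 1.15–1.25, with versus without mediators, is 25% vs 1% for diet, 8% vs 1% for inactivity and 69% vs 49% for alcohol.

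The comparison with and without mediators separates the two causes of elimination. For obesity it is almost wholly due to mediation. For alcohol, much of it is low power.

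**The case against.** A reader might infer that the upstream factors will lose most of their attributable risk or be dropped. The documents do not support that. They give no prevalence, no path strength and no OR for any modifiable factor, so every size above rests on assumptions. With direct ORs of 1.25–1.4 and moderate paths, elimination is 1% for obesity, 5% for diet and 0% for inactivity. Where the direct effect is nil, elimination near 95% is simply what a 5% test does to a null coefficient.

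A reader might also infer that the study's main result or its prevention message is undermined. The main aim is the genetic attributable fraction. The Abstract announces attributable risks without naming modifiable factors, and the closing paragraph of the Discussion argues from detection of polymorphisms and from the PRS combined with risk factors. The nine-factor list in the Discussion carries only a joint 90%, so a misranking of factors cannot be shown from it.

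It can further be said that the article speaks of models in the plural, that adjustment sets are often left to the analysis plan, and that confounders may be forced in. These replies carry less weight. The selection rule and the significance condition are stated, not omitted. Forcing in confounders does not help when the difficulty is that mediators are present, and Purposeful Selection is also data-driven.

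Two further objections stand and shape the remedy. Obesity may itself mediate diet and inactivity. And a prior diagnosis of hypertension or diabetes may have changed diet, activity or drinking, which would make it a confounder; leaving it out then adds bias of its own.

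**Conclusion.** The concern holds in limited form. Under the stated rules, the attributable risks of obesity, diet, inactivity and alcohol would be direct-effect remainders, understated to an unknown degree, and any of these factors may be eliminated and receive no figure. Under the assumed inputs the loss for obesity runs from about 27% to nearly 100%. It exceeds half at direct ORs up to 1.1, and at about 1.2 only with moderate or strong paths. For diet, inactivity and alcohol it is often under half. The direction rests on the assumption that these factors act partly through hypertension, diabetes and ApoB/ApoA1; the size rests on inputs that the documents do not give. The point is worth correcting before analysis, but it concerns additional outputs and not the main genetic attributable fraction.

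**What to change.** - Keep every risk factor listed under Variables in the models, with no univariate screen and no backward elimination. Report an attributable risk with 95% CI for each, whether or not its OR is significant.
- For obesity, diet, inactivity and alcohol, add a pre-specified model containing demographics, PRS and the factors judged to be confounders of that exposure. Leave out hypertension, diabetes and ApoB/ApoA1, and also obesity when the exposure is diet or inactivity. Label the result as a total effect.
- Report the fully mutually adjusted model beside it, labelled as a direct effect. State that a prior diagnosis of hypertension or diabetes may have changed behaviour, so that the two are to be read together.

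The cost is analysis wording and one extra table, with no new data. Attributable risks from different models cannot be added, and the report should say so.

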#### Estimation of population attributable risk

To characterize the study population, categorical variables will be described as counts and proportions and compared with Pearson’s chi-square test or with Fisher’s exact test [41]. Normally and asymmetrically distributed quantitative variables will be expressed as mean (standard deviation) or median (interquartile range), respectively [42]. Normality will be assessed by visually inspecting histograms and applying normality tests, if appropriate [43, 44]. Comparison of these continuous type variables will be carried out with Student’s t test for independent samples or Mann-Whitney test for non-parametric distribution [41].

All statistical analyses will follow the complete case analysis principle. All hypothesis tests will be 2-sided and p-value<0.05 considered statistically significant. Statistical data analysis will be conducted with SAS 9.4 (SAS Institute, Cary, NC).

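### The covariates behind the adjusted PRS estimate are left to p-value selection and unlisted investigator judgement, and no deciding model is named

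*Protocol article*

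**What the plan says.** All references are to the protocol article.

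- **Target.** The last paragraph of the Introduction sets the aim as the attributable fraction of the genetic profile, adjusted for modifiable risk factors. The Abstract promises adjusted odds ratios with 95% confidence intervals.
- **Covariates.** The Variables section says "Multiple logistic regression models will be built to adjust and determine the strength of association between demographic variables", traditional risk factors and the PRS. It lists sex, age and race, then nine further factors: smoking, diabetes, hypertension, obesity, anxiety and depression, diet, inactivity, alcohol and the ApoB/ApoA1 ratio. It calculates attributable risk only where the odds ratio is significant and does not say in which model.
- **Procedure.** Under Quantitative variables and statistical analysis, "univariate and multiple unconditional logistic regression analyses will be conducted". Covariates with univariate p<0.20 go forward to backward elimination, and the sample grows as variables drop out. Then: "Occasionally, covariates judged as confounding factors by the investigator may be forced into the final backward regression model". Finally: "Additional multiple logistic regression analyses may also be conducted using a variant of the Purposeful Selection algorithm".
- **Testing.** Under Estimation of population attributable risk, complete cases are analysed and "All hypothesis tests will be 2-sided and p-value<0.05 considered statistically significant".

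**The concern.** The study has one main question: how much of first ASCVD events is attributable to genetics once the listed risk factors are accounted for. The answer depends on what is in the model. The aim and the Variables section point to a known adjustment set, whereas the analysis section lets the data and later judgement decide it. A listed factor can be dropped because of its p-value, and an unlisted one can be added. A second algorithm may or may not be run. Nothing says that the PRS is exempt from elimination.

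Because attributable risk depends on a significant odds ratio, the choice of model can affect both the size of the genetic attributable fraction and whether it is calculated at all. A p-value and interval from a model chosen in this way do not carry their nominal 5% and 95% without qualification.

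**Working it through.** **1. What the planned test assumes.** The inputs, from Sample size calculation, are "odds ratio for genetics was set at 1.3, allele frequency of 10%, inheritance model was dominant", a disease prevalence of 10%, and "statistical power of 90%, type I error rate (α) of 0.05, 2-sided significance tests".

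- Carrier frequency = 1 − 0.9² = 0.19.
- With baseline odds solved for 10% prevalence, the carrier proportion is 0.2287 in cases and 0.1857 in controls (mean 0.2072).
- The likelihood-ratio information per case-control pair is 2[2H(0.2072) − H(0.2287) − H(0.1857)] = 0.00563, where H(p) = −p ln p − (1−p) ln(1−p).
- n = (1.960 + 1.282)² / 0.00563 = 1,866.7, that is 1,867 per group, as stated.

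The sample size is therefore right for one test at two-sided 0.05.

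**2. Target and procedure side by side.**

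| Item | Introduction / Variables | Analysis section |
|---|---|---|
| Listed risk factors | Adjusted for | Kept only if they pass p<0.20 and survive elimination |
| PRS | The exposure of interest | Not stated to be exempt from selection |
| Other confounders | None named | May be forced in; no list or rule |
| Selection method | None mentioned | Backward, optionally a second algorithm |
| Model behind the attributable risk | Not named | Not named |

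**3. The screen and balanced covariates.** Under Eligibility criteria, cases and controls are recruited 1:1 with adjustment for sex and age. A covariate with no case-control difference has a uniform p-value, so it fails a p<0.20 screen with probability 1 − 0.20 = 80%, and more often if balance is enforced. If recruitment achieves balance, sex and age will usually be screened out. They would then return only through discretionary forcing.

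**4. Size of the effect on type I error.** Three simulations used 1,867 cases and 1,867 controls, 12 covariates, and a PRS with no independent effect that was kept in every model so that its p-value could be read. There were 1,500 runs per setting, with Monte Carlo SE of about 0.6 to 0.7 points. The adjusted routes were the full list, backward elimination, backward with forced covariates, and a form of Purposeful Selection. Covariate effects, correlations, missingness completely at random in the nine non-demographic covariates, and thresholds the article does not give were all assumed.

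| Chance that any adjusted route gives p<0.05 | No missing | 2% missing per covariate | 5% missing per covariate |
|---|---|---|---|
| Simulation A (forces in each dropped covariate in turn, and all together) | 5.0-5.7% | 7.9% | 8.3-8.7% |
| Simulation B (PRS unrelated to covariates) | 5.5% | not run | not run |
| Simulation C | 5.9% | 7.1% | 7.3% |

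In B, each adjusted model alone rejected in 5.2-5.3% of runs. With the PRS correlated 0.2 with one risk factor (800 runs), any adjusted route rejected in 4.3%. With complete data the selection algorithm changes little. The rise with missing data arises because the models then use different participants. In C the full, backward and Purposeful models disagreed on significance in 0.5%, 1.7% and 2.9% of runs at 0, 2 and 5% missing. In A the figure was about 3-4% at 2-5% missing.

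**5. Cost of a fixed model under complete cases.** Assume independent missingness in nine covariates.

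- 2% each: 0.98⁹ = 0.83 kept; interval wider by 1/√0.83 ≈ 1.10.
- 5% each: 0.95⁹ = 0.63 kept; interval wider by 1/√0.63 ≈ 1.26.

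**The case against.** The strongest reply is that the text describes one sequence: univariate screen, backward elimination, recognised confounders retained, then an optional supplement. Much of this stands. Univariate analysis is mainly the screening step, and the Abstract and Introduction make the adjusted estimate the target. Backward elimination with forcing is one procedure, and Purposeful Selection is introduced as additional. The Variables list may be the candidate set and not a separate model. Forcing in confounders need not follow a look at the PRS result, although nothing requires the decision to be made beforehand.

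A reader might therefore infer too much in three ways.

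- **Five rival models.** The text does not support this, for the reasons just given. Nor does the familywise figure of 1 − 0.95⁵ = 22.6% apply, because the models share nearly all their data.
- **The univariate rejection rate.** In simulation A, with a PRS correlated 0.1 with ApoB/ApoA1 and no independent effect, the univariate model is significant in 33-36% of studies. That is a real marginal association correctly detected. It is not error inflation.
- **A large loss of error control.** The 7-9% figures need assumed missingness and count a rejection by any adjusted route, which is a worst-case search.

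It may also be said that the full protocol (S2 File) or an analysis plan, neither of which is shown, could name the primary model. That is possible. But the point rests on rules the article states: selection by p-value, discretionary forcing, and a significance condition on the main estimate. These conflict with its own target of adjustment for listed factors.

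**Conclusion.** The concern holds in limited form. The aim requires adjustment for listed factors, and the stated procedure can remove them, does not protect the PRS, and leaves later additions to judgement. The model that supplies the attributable fraction is not named. The main estimate can therefore rest on an adjustment set chosen after the data are seen.

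The numerical effect on type I error is small: about 5-6% with complete data and about 7-9% across adjusted routes at 2-5% missing per covariate. These figures depend on assumed covariate effects, thresholds and missing-data rates, and on the PRS being kept in every model. What happens if the PRS itself is exposed to elimination was not simulated. The case for change rests more on whether the main estimate matches the stated aim than on error inflation. It should be corrected, but it does not undermine the design.

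**What to change.** In the analysis section, name one deciding logistic model for the genetic question:

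- The PRS is always retained. The covariates are those of the Variables section, including sex and age, plus any further confounders the investigators want, all listed before genotype is linked to case status.
- No univariate screen, elimination or later forcing applies to this model.
- The PRS odds ratio, p-value and attributable fraction come from this model.
- The backward-elimination and Purposeful Selection models are labelled sensitivity analyses, and all that are run are reported.

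This is a change of wording, and the sample size stays at 1,867 per group. Twelve covariates are few for 1,867 cases, so selection is not needed to protect precision. The real cost is participants: at the assumed missing rates, complete-case analysis of the fixed model loses about 17% or 37%, more than a reduced model would. Either state the number analysed in each model, or impute missing covariates in the deciding model. The sensitivity models should not be confined to the deciding model's complete cases, since that would discard data they can use.
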